### Ergonomic assessment

Satisfaction and adherence will be evaluated 6 months (T2) after baseline measurements.

A lack of adherence to programs aiming at increasing PA in tertiary employees has been reported multiple times [107, 108]. Genin et al. postulated that interventions targeting PA and SB in tertiary employees should not only consider the operational feasibility but also the coherence and compatibility with the working environment, structuration, functioning as well as the workers and the way they live and experience their work [24]. Therefore, an ergonomic approach is needed to improve the implementation of such an intervention in future studies but also to optimize future guidelines on strategies to reduce SB in tertiary worksite.

A satisfaction questionnaire will be given to all participants at the end of the program. A one-on-one interview will be done by an ergonomic specialist with each participant. This interview will aim to better understand (1) how PA on the workstation has been conciliated with the work tasks performed by the subject and (2) reasons of subject’s involvement in the prescription of PA. To achieve this objective, an analysis of the subject’s diary will be carried out as well as a direct, semi-direct or open interview on the participant’s motivations. These interviews will be recorded with the permission of each participant. These recordings are essential for the analysis of the verbal data collected.

### Sample size and power calculation

Sample size estimation is based on CONSORT 2010 statement for the comparison between randomized groups. In these statements, Eldridge et al. suggested “that the size of a trial should be related to the size of the future definitive RCT and for such a trial designed with 90% power and two sided 5% significance” [109]. They “recommend trial sample sizes for each treatment arm of 75, 25, 15, and 10 for standardized effect sizes that are extra small (0.1), small (0.2), medium (0.5), or large (0.8), respectively”. Considering a two-sided type I error at 5% and a statistical power greater than 80%, an effect size of 1 can be assumed for the PA and SB levels score with 18 patients per group. To take into account the lost to follow-up, a maximum of 80 patients (20 by arm, 50% females) will be included in the study.

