## Methods and analysis

### Study design

The REMOVE study is a prospective, exploratory, randomized, controlled, open-label, multicentre, two-arm parallel trial in office-sitting desk workers (Fig. 1).

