**Fig. 1 Fig1:**
[figure not shown]
Study overview

Eighty tertiary employees from Clermont-Ferrand (France) will be recruited to participate in this protocol. Three worksites of moderate size (*n* = 80 employees across the 3 sites) will be randomly assigned to one of the two interventions: (1) CTL_PPM3, an intervention with two consecutive periods: 3 months with no change of working conditions (CTL: control phase) and 3 months of PPM use (PPM3), and (2) PPM6, an intervention with 6 months of PPM use. Tests will be performed on both groups at baseline (T0), after 3 (T1) and 6 months (T2) of the intervention. Information sheets will be given to all the participants and written informed consent will be obtained for each participant. This study has been approved by the ethical authorities (CPP IDF VIII 19 09 66) and registered as a clinical trial under the reference number NCT04153214 (clinicaltrials.gov).

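### Eighty participants in a two-arm 1:1 trial cannot be 20 per arm: the enrolled total and the per-arm number contradict each other, and no loss rate is given to settle it.

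*Protocol article*

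**What the plan says.** All references are to the protocol article.

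- **Sample size and power calculation, requirement.** "Considering a two-sided type I error at 5% and a statistical power greater than 80" per cent, the article states that "an effect size of 1 can be assumed for the PA and SB levels score with 18 patients per group".
- **Same section, enrolment.** To cover loss to follow-up, for which it gives no rate, "a maximum of 80 patients (20 by arm, 50% females) will be included in the study".
- **Same section, stated basis.** The estimate is said to rest on published guidance for trials that precede a definitive one, under which "the size of a trial should be related to the size of the future definitive RCT". The per-arm sizes quoted from it are 75, 25, 15 and 10, for standardized effects of 0.1, 0.2, 0.5 and 0.8.
- **Study design.** This is a "two-arm parallel trial in office-sitting desk workers". The text below Figure 1 adds: "Eighty tertiary employees from Clermont-Ferrand (France) will be recruited to participate in this protocol". The same paragraph repeats 80 as the number across the three worksites, and the abstract also gives N = 80.
- **Randomization.** Allocation is 1:1, stratified by centre.

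**The concern.** The total and the per-arm count stand in the same sentence and cannot both be right for a two-arm trial with equal allocation. The enrolled number is a core design figure: it shows how much attrition was planned for and how small an effect the trial could be expected to detect. The two readings differ by a factor of two in size, and they imply very different loss allowances. Attrition is a live issue here, because the Discussion reports substantial dropout in the team's earlier worksite programmes. A reader who takes the parenthesis at face value will think the trial half as large as the rest of the article says.

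**Working it through.** **Inputs.** Two-sided alpha 0.05, power above 80%, standardized effect d = 1, and 18 evaluable per group (Sample size section). Two arms (abstract, Study design). Allocation 1:1 (Randomization). Student's t test for the primary comparison (Statistical analyses). Total 80, and 20 by arm (Sample size section).

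**Step 1: reproduce the plan's own figure.** The normal formula per group is n = 2(z₀.₉₇₅ + z₀.₈₀)²/d² = 2(1.960 + 0.842)²/1² = 15.7, rounded up to 16. The exact t-based solution is 16.7, rounded up to 17. With n = 18 the noncentrality is d√(n/2) = 1 × √9 = 3.0 on 34 degrees of freedom, and power is 83.0% (85.1% by the normal approximation). The claim of "a statistical power greater than 80" per cent "with 18 patients per group" is correct.

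**Step 2: arm arithmetic.** 2 × 20 = 40, not 80. At 1:1, 80/2 = 40 per arm.

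**Step 3: implied loss from 18 evaluable.**

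- 20 per arm: 1 − 18/20 = 10%, and 18/0.90 = 20 exactly.
- 40 per arm: 1 − 18/40 = 55%.

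**Step 4: what each size delivers.** Two-sample t test, two-sided 5%, exact noncentral t:

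| Per arm | Power at d = 1 | Effect detectable with 80% power |
|---|---|---|
| 18 (stated requirement) | 83.0% | 0.96 SD |
| 20, before loss | 86.9% | 0.91 SD |
| 40, before loss | 99.3% | 0.63 SD |

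The detectable effects at 20 and 40 per arm differ by 0.909 − 0.634 = 0.275 SD.

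**Step 5: the stated basis.** The quoted guidance offers 75, 25, 15 or 10 per arm. None of 18, 20 or 40 is on that list. The 18 comes from the separate power statement for d = 1, so describing the size as based on the guidance does not match how it was obtained.

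**The case against.** The best defence is that nearly everything in the article points the same way. Eighty appears in the abstract, in the design section and in the sample size section; two arms and 1:1 allocation are stated plainly. Only one parenthesis disagrees. It may be a garbled 20 per sex per arm, since the same parenthesis says half will be women and 2 × 2 × 20 = 80; or it may be left over from a four-group layout (4 × 20 = 80). At 80, the trial also exceeds its stated need of 18 per group.

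Much of this stands. It makes 40 per arm the likelier intent, and it means that the error does not leave the trial too small for its stated effect. It does not remove the contradiction. Neither reconciling reading is written anywhere, the printed count is per arm, and calling 80 a maximum does not help because the parenthesis describes that same 80. Nor is this a detail left to a fuller document: the article prints two figures that conflict.

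Several stronger readings are tempting, but the article does not support them:

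- **That the power claim is wrong.** It is not; 18 per group at d = 1 gives 83.0%.
- **That 90% and 80% power contradict each other.** The 90% sits inside the quoted guidance and describes the future definitive trial. This trial's own power is set in the next sentence.
- **That a null result could not be interpreted.** The primary result is to be reported as an effect size with a 95% confidence interval, which shows what effects are excluded whatever the planned power.
- **That the trial is underpowered for an hour less sitting per day.** That needs a standard deviation in minutes, and the article gives none. The baseline-adjusted model would also change the answer.

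**Conclusion.** The point holds as an internal contradiction in the sample size. A total of 80 and 20 per arm cannot both describe a two-arm 1:1 trial. The recurrence of 80 makes 40 per arm the likelier intent, but that is an inference, because the article never states it.

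In size, the readings are 40 versus 80 people, 10% versus 55% implied loss, 86.9% versus 99.3% power at d = 1, and 0.91 versus 0.63 SD detectable with 80% power. The power and detectable-effect figures assume a two-sample t test at two-sided 5%, full retention and no baseline adjustment. The implied loss rates assume that 18 per group is the evaluable target, as the section presents it.

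The wording of the justification is a lesser fault: the guidance does not produce the numbers used.

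This needs correcting because it misstates a figure the trial relies on. It is not evidence that the trial is too small for the effect it names.

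**What to change.** 1. State one total with the matching number per arm. If the total is right, that is 80 participants, 40 per arm; if 20 per arm was truly intended, the total must become 40 wherever it appears.
2. Give the loss rate actually assumed at planning. It should not be back-calculated: the 10% follows only from the 20-per-arm reading, so applying it to 40 per arm would mix the two readings.
3. Restate the power or detectable effect that follows from the corrected number and that loss rate. Trial status says recruitment finished on 15 March 2021, so any figure not fixed at planning, including the 0.63 SD above, must be labelled as calculated afterwards.
4. Reword the statement that the size is based on the pilot-trial guidance, and say that 18 per group comes from the power calculation for a standardized effect of 1.

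The cost is a correction to the text. No extra participants, measurements or changes to the analysis are needed.

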### Statistical analyses

Statistical analyses will be conducted using Stata software (version 15, StataCorp, College Station, USA). A two-sided *p* value of less than 0.05 will be considered to indicate statistical significance. Participants will be described at baseline and between-group comparison will be tested using an unpaired *t* test for the following variables: compliance with eligibility criteria, demographic characteristics, clinical characteristics and medication. A possible difference between groups in any of these characteristics will be determined by both clinical and statistical considerations. The number of patients included and the inclusion curve will be presented by group.

The primary endpoint (time spent in PA and SB) will be compared between groups by Student’s *t* test or the non-parametric Mann-Whitney test if assumptions of parametric tests are not met. The normality will be studied using Shapiro-Wilk test. The homoscedasticity will be analysed with Fisher-Snedecor test. The results will be expressed using effect size and 95% confidence interval. Intention-to-treat analysis will be considered for the primary analysis. In order to prevent attrition bias, imputation of the missing data is planned. The statistical analysis plan also provides for an additional per-protocol analysis. Then, the analysis of the primary outcome will be completed by multivariable analysis using a linear mixed model to compare PA and SB score between randomized groups taking into account (i) covariates determined according to univariate results and to clinical relevance (gender, age and baseline PA and SB) and (ii) centre as random-effects (to measure between- and within-centres variability). The normality of the residuals from linear regression will be studied. If necessary, a logarithmic transformation of the dependent variable will be proposed. The results will be expressed using effect-sizes and 95% confidence intervals.

The comparisons between the randomized groups will be performed (1) as aforementioned for continuous secondary endpoints and (2) using the chi-squared or Fisher exact tests for categorical variables. For non-Gaussian data, results will be presented using median difference and 95% confidence intervals estimated using quantile regression model. For categorical parameters, the results will be expressed using absolute differences and 95% confidence intervals. The multivariable analysis associated to dichotomous endpoints will be generalized linear mixed model, with logit link function, and centre as random-effect. As secondary endpoints will be exploratory, no type I error correction will be applied, but the results will be expressed with odds ratios and 95% confidence intervals.

Longitudinal data will be analysed using random-effects regressions, modelling between and within patient effect, as random-effect, in addition to centre effect. The following fixed effects will be studied: randomization group, time-points evaluation and their interaction.

According to clinical relevance and to the European Medicines and Consolidated Standards of Reporting Trials recommendations, planned subgroup analyses will be proposed after completion of the study. *Subgroup × randomization group* interaction will be added to the in regression models with factors such as gender or age used for the subgroup analysis.

Particular attention, mainly descriptive, will be paid to study the adherence of participants and identify barriers and challenges to their motivations and ability to perform the PA intervention. A sensitivity analysis will be performed to study the statistical nature of missing data and to determine the most appropriate approach to the imputation of missing data: maximum bias (e.g. last observation carried forward, baseline observation carried forward) or estimation proposed by Verbeke and Molenberghs for repeated data. A study of patients’ abandoning will be proposed considering this parameter as a censored data, and consequently using the Kaplan-Meier to estimate it and log-rank for the comparison between groups.

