### Data collection

All measurements will be performed on three different occasions: baseline (T0), 3 months (T1) and 6 months (T2). Figure 1 and Table 1 present the overall study. All the clinical measurements will be done at the Laboratory of the Metabolic Adaptations to Exercise under Physiological and Pathological Conditions, in Clermont-Ferrand (France).

**Table 1 Tab1:** Measurements timeline for both groups

Measurements timeline for both groups			
Measurement	Baseline	3 months	6 months
Socio-demographic data	X		
Objectively measured of PA and SED	X	X	X
Self-reported lifestyle behaviours	X	X	X
Health-related outcomes	X	X	X
Body composition	X	X	X
Physical fitness	X	X	X
Metabolic outcomes	X	X	X
Stress and anxiety	X	X	X
Life span and quality	X	X	X
Resting metabolic rate	X	X	X
Satisfaction and adherence			X

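### Continuous secondary endpoints: the text does not put each endpoint's own T0 value into its between-group comparison

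*Protocol article*

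**What the plan says.** All references are to the protocol article.

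- **Primary outcome, first step** (Statistical analyses): the activity and sedentary times "will be compared between groups by Student’s *t* test or the non-parametric Mann-Whitney test if assumptions of parametric tests are not met".
- **Primary outcome, second step** (same section): "the analysis of the primary outcome will be completed by multivariable analysis using a linear mixed model to compare PA and SB score". The model has centre as a random effect and "covariates determined according to univariate results and to clinical relevance (gender, age and baseline PA and SB") as covariates. This is the only covariate list in the article.
- **Continuous secondary endpoints** (same section): comparisons are "performed (1) as aforementioned for continuous secondary endpoints". No covariates are named for them.
- **Repeated measures** (same section): "Longitudinal data will be analysed using random-effects regressions, modelling between and within patient effect, as random-effect, in addition to centre effect". On the terms of that model the article adds: "The following fixed effects will be studied: randomization group, time-points evaluation and their interaction".
- **Status of these endpoints** (same section): "As secondary endpoints will be exploratory, no type I error correction will be applied".
- **Availability of T0 values** (Data collection): "All measurements will be performed on three different occasions: baseline (T0), 3 months (T1) and 6 months (T2"). Table 1 lists body composition, physical fitness, metabolic outcomes, and stress and anxiety at all three visits.

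**The concern.** In the primary model, baseline PA and SB are the outcome's own starting values, so the covariate list suits that outcome. Carried by reference to body composition, fitness, blood markers or psychological scales, the same list offers only an indirect predictor. The best available predictor of a T1 value is usually the same measurement at T0.

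The back-reference can be taken in two literal ways. It may cover only the choice between the t test and Mann-Whitney, in which case there is no adjustment. It may also cover the mixed model, in which case the named covariates are gender, age and baseline PA and SB. In neither case does the endpoint's own T0 value enter the between-group comparison.

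At stake is the width of the confidence intervals for the secondary objective. A chance T0 difference in an endpoint would also carry into its T1 comparison, while the longitudinal model for the same endpoint would account for it. The article does not say which of the two is the reported T1 effect.

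**Working it through.** **1. The plan's own figure.** The sample size section gives 18 per group for an effect size of 1, two-sided 5% error and power above 80%. The normal approximation gives 16 per group and the exact t test 17. Power at 18 per group is 0.83 by the t test, so the figure reproduces. It concerns the primary outcome and does not settle the covariate question.

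**2. Inputs.** The T0-T1 correlation r of each secondary endpoint is not in the documents. It is an assumption, shown at 0.5, 0.7 and 0.9. Detectable effects use 40 per arm (80 participants at 1:1). The sample size section also mentions 20 by arm, so that size is shown too. The variance factors do not depend on the number per arm.

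**3. Formulas.** Variance of the T1 group difference, relative to the unadjusted comparison (set to 1), with equal variances and complete data:
- adjusted for the endpoint's own T0 value: 1 − r²
- group-by-time contrast between T0 and T1: 2(1 − r)

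| r | Own T0: 1 − r² | Variance cut: r² | Group × time: 2(1 − r) | Group × time relative to own T0: 2/(1 + r) |
|---|---|---|---|---|
| 0.5 | 0.75 | 25% | 1.00 | 1.33 |
| 0.7 | 0.51 | 49% | 0.60 | 1.18 |
| 0.9 | 0.19 | 81% | 0.20 | 1.05 |

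**4. How much the longitudinal model recovers.** Its gain over the unadjusted comparison, as a share of the own-T0 gain:
- r = 0.5: (1 − 1.00)/0.25 = 0%
- r = 0.7: (1 − 0.60)/0.49 = 82%
- r = 0.9: (1 − 0.20)/0.81 = 99%

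Below r = 0.5 the contrast is less precise than no adjustment; at 0.3 its factor is 1.4.

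**5. Check by simulation.** There were 4,000 runs with 40 per arm and equal correlation between visits. Baseline PA/SB was assumed to correlate 0.2 with the endpoint's T0 value. Standard errors of the T1 difference, in SD units:

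| r | Unadjusted | PA/SB covariate | Own T0 | Group × time |
|---|---|---|---|---|
| 0.5 | 0.225 | 0.226 | 0.194 | 0.223 |
| 0.7 | 0.221 | 0.221 | 0.161 | 0.174 |
| 0.9 | 0.223 | 0.219 | 0.096 | 0.098 |

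Under that assumption the PA/SB covariate does almost nothing. Even a correlation of 0.2 with the T1 value itself would cut the variance by only 0.2² = 4%.

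**6. Detectable effect at 80% power.** The unadjusted value is multiplied by √(1 − r²), which is 0.866, 0.714 and 0.436.
- 40 per arm: 0.63 SD unadjusted; 0.55, 0.45 and 0.28 SD with own T0.
- 20 per arm: 0.91 SD unadjusted; 0.79, 0.65 and 0.40 SD with own T0.

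**The case against.** The covariate list sits in a sentence about the primary outcome. A sympathetic reader takes the back-reference to carry over a method, namely adjustment for gender, age and the baseline of whatever is being analysed. The stated selection rule, univariate results and clinical relevance, would also tend to pick a strong predictor such as the endpoint's own T0 value. Endpoint-specific covariates are often left to a statistical analysis plan; the article mentions one, and it is not shown. The longitudinal model already uses T0 values as responses. The trial and its secondary endpoints are labelled exploratory.

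Much of this stands. A reader might infer that the plan deliberately adjusts secondary endpoints for baseline PA and SB instead of their own baseline. The text does not say that, and it does not exclude the T0 value. Nor does chance imbalance at T0 bias the comparison: under randomisation the cost is precision.

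Two parts do not fully answer the point. The by-analogy reading is plausible but unwritten, and relying on univariate results leaves the covariate to be decided from the data, endpoint by endpoint. The longitudinal model is a near-complete remedy only at high correlation; at 0.5 it gives essentially nothing over the unadjusted test.

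**Conclusion.** The point holds as a free improvement. As written, nothing places each continuous secondary endpoint's own T0 value in its between-group comparison, and doing so is better than either an unadjusted test or a model adjusted for baseline PA and SB.

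The variance reduction at stake is about 25%, 49% or 81% at assumed correlations of 0.5, 0.7 or 0.9. What remains after the planned group-by-time model is a variance 1.33, 1.18 or 1.05 times that of own-T0 adjustment. These figures rest on assumed correlations, equal variances across visits and complete data.

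A reader might go further and conclude that the adjusted comparisons lose most of their available precision. The documents do not support that: it needs r² above one half, that is r above about 0.71, and it overlooks the longitudinal model, which recovers nearly all of the gain where the correlation is high.

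**What to change.** In Statistical analyses, state that the adjusted mixed model for each continuous secondary endpoint uses the T0 value of that same endpoint in place of baseline PA and SB, together with gender, age and centre. State also that this adjusted T1 difference, with its 95% confidence interval, is the one reported. If the endpoint is log-transformed, as the section allows, enter its T0 value on the same scale.

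The cost is one or two sentences, settled before the data are analysed; no measurement or participant is added. The second sentence does make a choice, because it puts the adjusted difference ahead of the unadjusted test for these exploratory endpoints. If the statistical analysis plan already specifies own-baseline adjustment, only the wording of the protocol needs to be aligned.

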#### Randomization

A permuted-block randomization (i.e. random block sizes) will be conducted by the study biostatistician using a computer-generated random allocation (Stata software, version 15, StataCorp, College Station, US), with a 1:1 ratio allocation, ensuring complete randomness of the assignment of a patient to each randomized group. The randomization will be stratified by centre. The randomization and allocation process will be performed by the statistician involved in this study. Physicians will be involved for the enrolment participants.

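### The longitudinal model leaves the two arms' T0 means free, so its 3- and 6-month group-by-time effects are raw differences in change: unbiased, but less precise than the data allow

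*Protocol article*

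**What the plan says.** The Data collection section sets the occasions: "All measurements will be performed on three different occasions: baseline (T0), 3 months (T1) and 6 months (T2"). Table 1 places nearly every outcome at all three.

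The Statistical analyses section then handles baseline in three ways:

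- **Primary comparison.** The two activity measures "will be compared between groups by Student’s *t* test or the non-parametric Mann-Whitney test if assumptions of parametric tests are not met". No baseline term is mentioned.
- **Multivariable mixed model for the primary outcome.** It has centre as a random effect and "covariates determined according to univariate results and to clinical relevance (gender, age and baseline PA and SB") as adjustment. Continuous secondary endpoints are referred back to these methods.
- **Longitudinal model.** "Longitudinal data will be analysed using random-effects regressions, modelling between and within patient effect, as random-effect, in addition to centre effect". For its fixed part: "The following fixed effects will be studied: randomization group, time-points evaluation and their interaction". It lists no baseline covariate and no constraint on the T0 means.

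The Randomization section describes individual allocation "with a 1:1 ratio allocation, ensuring complete randomness of the assignment of a patient to each randomized group", and adds: "The randomization will be stratified by centre". The Study design section, by contrast, says that three worksites will be randomly assigned to the interventions.

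**The concern.** If T0 is a level of the time factor, the group main effect is a free difference between the arms at T0. When participants are randomised individually, any such difference is chance. Estimating it as a parameter makes the T1 and T2 interaction terms equal, with complete data, to the difference between arms in mean change from T0. A change score subtracts the whole T0 value, whereas the most precise use of T0 subtracts only the part that predicts follow-up. The T0 data are therefore collected and modelled, but used in an inefficient form.

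At stake is the width of the intervals for the 3- and 6-month effects in the repeated-measures analysis, in a small trial. There is also an inconsistency. The multivariable model and the longitudinal model each yield a 3-month group contrast for PA and SB, one adjusted for baseline and the other a difference in change.

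**Working it through.** **Inputs from the protocol article.** Three occasions (Data collection). Fixed effects of group, time and their interaction, with participant and centre random effects (Statistical analyses). 1:1 allocation stratified by centre (Randomization). Effect size 1 with 18 per group, "Considering a two-sided type I error at 5% and a statistical power greater than 80"% (Sample size and power calculation).

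**Assumptions.** ρ is not given, so 0.3 to 0.9 is shown. Complete data, equal SD σ at each occasion, and compound symmetry, as a participant random intercept implies. Centre is left out: with allocation balanced within centre, a centre intercept does not change the comparison, and ρ is then the within-centre correlation.

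**The plan's own figure.** Effect size 1, two-sided 5% and 80% power need 16 per group by the normal approximation and 17 by the t test. At 18 per group the t test has power 0.83. The stated figure reproduces.

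**Planned model (free T0 means).** The T1 interaction is (mean T1 − mean T0) in one arm minus the same in the other. Each arm contributes 2σ²(1−ρ)/n, so the variance is 4σ²(1−ρ)/n, that is 2(1−ρ) in units of 2σ²/n. A random-intercept mixed model fitted to simulated complete data gave an interaction of 0.71376, identical to the raw difference in mean change.

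**Common T0 mean, or T0 as covariate (large sample).** The variance is 2σ²(1−ρ²)/n, that is 1−ρ² in the same units.

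**Ratio, planned to common.** 2(1−ρ)/(1−ρ²) = 2/(1+ρ). Generalised least squares for two arms and three occasions confirmed both formulas; for example, at ρ = 0.5 and 20 per arm, with σ = 1, the variances are 0.100 and 0.075. The T2 contrast gives the same values.

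| ρ | Planned 2(1−ρ) | Common T0 mean 1−ρ² | Variance ratio | Planned SE larger by |
|---|---|---|---|---|
| 0.3 | 1.40 | 0.91 | 1.54 | 24% |
| 0.5 | 1.00 | 0.75 | 1.33 | 15% |
| 0.6 | 0.80 | 0.64 | 1.25 | 12% |
| 0.7 | 0.60 | 0.51 | 1.18 | 8.5% |
| 0.9 | 0.20 | 0.19 | 1.05 | 2.6% |

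A comparison of follow-up values alone has factor 1, so below ρ = 0.5 the planned interaction is less precise than ignoring T0.

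**Illustrative power, planned v common T0 mean**

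| ρ | Effect 1, 18 per arm (noncentral t) | Effect 0.5 (assumed), 40 per arm (normal approximation) |
|---|---|---|
| 0.3 | 69% v 86% | 47% v 65% |
| 0.5 | 83% v 92% | 61% v 73% |
| 0.7 | 96% v 98% | 82% v 88% |

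The second column takes 80 participants split over two arms.

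**T2 minus T1.** Under compound symmetry Cov(Y2−Y1, Y0) = ρσ² − ρσ² = 0. T0 carries no information on this contrast, and the gain is zero.

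**Cost of estimating the slope on T0.** An inflation of 1 + 1/(2n−4) at n = 18 is 1 + 1/32 = 1.031. The adjusted factors become 0.94, 0.77, 0.53 and 0.196 at ρ = 0.3, 0.5, 0.7 and 0.9, still below 1.40, 1.00, 0.60 and 0.20.

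**The case against.** The strongest reply is that the listed model is a standard and valid specification, and that the plan already contains a baseline-adjusted analysis. Both points are true. The multivariable mixed model adjusts PA and SB for baseline, and the cross-reference for continuous secondary endpoints arguably carries that approach over. A reader might infer from the longitudinal model that the plan never adjusts for baseline, or that the primary analysis is weakened; the document supports neither. What remains is that the adjustment is not carried into the longitudinal model.

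A reader might also infer bias, because an arm that starts worse by chance will tend to appear to improve more. That holds only conditionally on an observed imbalance. Over repeated randomisations the difference in change is unbiased, and its intervals already reflect the chance.

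Third, the article does not say outright that T0 is a response level, and the parameterisation could be left to a separate analysis plan. But the fixed effects are stated, and T0 is one of only three occasions. If T0 were left out of the response, the listed terms would use no baseline information: the factor would be 1 against 1−ρ², so precision would be lost in another form.

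Fourth, the sample size section sizes a two-group comparison, not the interaction, and the trial calls itself exploratory. So the power table illustrates the loss and does not show a missed design target. The effect of 0.5 is an assumption, as is ρ.

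Fifth, the hypothesis of further improvement from 3 to 6 months concerns the change after T1. Under compound symmetry that contrast gains nothing. This stands in full.

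**Conclusion.** The point holds as one of efficiency and consistency, confined to the T1 and T2 group-by-time effects of the longitudinal model. Their variance exceeds that under a common T0 mean by the factor 2/(1+ρ). This is material for ρ between 0.3 and 0.6 (variance 54% to 25% larger) and negligible near 0.9. The exact equality with a difference in change needs complete data and is approximate with missed visits. The claim that adjustment never costs precision is strict only with a known covariance. At 18 per arm the inflation above breaks even at ρ = 2/1.031 − 1, about 0.94, where little is at stake either way.

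The common T0 mean rests on the individual 1:1 allocation in the Randomization section. If worksites were the units allocated, as Study design states, arms built from three sites could differ materially at T0 and the constraint would be hard to defend.

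**What to change.** First reconcile the Study design and Randomization sections on whether worksites or individuals are randomised.

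Then, if individuals are, specify the repeated-measures model in Statistical analyses in one of two ways:

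- a common T0 mean: fixed effects of time, group × T1 and group × T2, no group effect at T0, with the participant and centre effects kept; or
- T1 and T2 as the responses, with that outcome's own T0 value as covariate, plus centre.

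Either makes the model's 3- and 6-month contrasts baseline-adjusted, in line with the multivariable model for PA and SB.

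The cost is about one sentence of analysis wording, once the unit of randomisation is settled, and no new data. The small downside is that the reported contrast is a baseline-adjusted difference and not a simple difference in change, which the results text should say.
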